#### Phase 2: implementation

Although the precise procedures will only be known by completing phase 1, the general procedures will be as follows: The RA will identify, with the assistance of a ward clerk or clinic nurse, those patients of the participating oncologists that meet the eligibility criteria. The RA will contact the patient prior to the consultation day to explain the study and obtain verbal informed consent. The RA will check to see whether or not the patient has access to a computer for the purpose of listening to the recorded consultation. An analog recording will be offered to patients without access to a computer. On the day of the consultation, the RA will greet the patient in the waiting area to acquire written consent to participate and complete the Patient Sociodemographic and Disease Information Form. The RA will inform the oncologist or primary nurse that a patient who is participating in the implementation study has arrived and will ensure that the recording materials are in place. The exact delivery mode for the recording of the consultations will be tailored to each location during the implementation study. With audiotape use becoming obsolete, however, and based on feedback during the preliminary phase, we plan to record each consultation with a hand-held digital recorder and then immediately download the consultation to either a USB key (*i.e.*, memory stick) that is handed to the patient or a website for the patient to access with a passcode. Given that valuable information is commonly imparted to the patient by the primary nurse during the initial consultation, the consultation with the oncologist and the consultation with the primary nurse will be recorded. The RA will meet the patient after the consultation to provide a copy of the consultation recording or explain how she or he may gain access to the recording via computer. The RA will contact the patient two days postconsultation by telephone to find out whether the recording was listened to and to administer the Digital Recording Use Semi-Structured Interview (DRUSSI) [1,2] if this is the case. The patient will be contacted again at seven days postconsultation to administer the DRUSSI once more. The DRUSSI has evolved over successive research studies conducted by the team. Although we coined the term DRUSSI for the current proposal, we first used a variant of the DRUSSI (referred to then as the Audiotape Questionnaire) in the late 1990s in a pilot study for a larger randomised controlled trial (RCT) we conducted with women with breast cancer. For our two RCTs conducted with breast and prostate cancer patients, this instrument was called the Audiotape Use and Satisfaction Questionnaire. New to the DRUSSI for the current proposal are questions #2 ('When did you listen to the recording?'), #5 ('When did you make your treatment decision?'), and #6 ('Did the recording assist in making your treatment decision?'). The estimated maximum time for completion of the DRUSSI is 20 minutes. It is expected that each of the interviews (two days and seven days postconsultation) will not exceed 30 minutes.

Nearing the close of the final patient interview, the RA will invite those patients who listened to the recorded consultation to share their consultation-recording experience with the oncologist/nurse as a way of providing facilitative feedback. For willing patients, the RA will prepare a letter on behalf of the patient based on responses to the DRUSSI. The RA will make arrangements for the patient to suggest changes to the letter. The RA will ask the patient to sign the letter before the RA brings it to the oncologist/nurse (or the patient may choose to give the letter to the oncologist/nurse). Just prior to ending the interview, the patient will be invited to attend a focus group of the patients who participated in the implementation study at that location. This focus group will be held in a meeting room at the site within two months following completion of the final patient interview at each location, that is, in phase 3 (below). The goal of the focus group is to provide feedback and learn more about the patients' consultation-recording experiences. A local patient advocate for the disease site (breast or prostate) will be invited to attend the focus group in an effort to promote the intervention. The RA and the PI will lead the focus groups; each focus group will be recorded and transcribed, and the transcript will be reviewed to identify salient points. The local site coordinator will contact the oncologist and primary nurse after five of their patients have participated, for the purpose of finding out if the study is progressing smoothly, to document oncologist/nurse feedback on their participation in the study, and to address any concerns. The aim is to identify and remedy as quickly as possible any unforeseen events or circumstances that might hamper the successful implementation of the intervention. The local site coordinator will maintain a log book to keep a written record of these events and circumstances and the actions taken to address them.

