#### Phase 1: preimplementation

The oncologists who are serving as local site coordinators will hire a research nurse associate (RA) for their particular location. A team meeting will then be scheduled to make any necessary modifications to the implementation protocol. The most important product of this meeting will be a detailed sequence of implementation steps that will be followed prior to launching the consultation-recording intervention in phase 2. The RAs will be invited to this meeting so they can meet each other and receive training. Subsequent to this team meeting and at quarterly intervals, the principal investigator (PI) will hold a conference call with the RAs to address any concerns and provide encouragement.

Prior to launching phase 2, the PI will travel to each location to introduce the study at either grand rounds or disease site rounds. The PI will then meet with each participating oncologist and primary nurse for a short, recorded interview. At the interview, the results of the prestudy contextual readiness assessment will be shared, the implementation plan will be reviewed, feedback with respect to the plan will be elicited, and the oncologist/nurse will be asked to sign an informed consent form. The PI will also interview other clinic staff--nurses, oncology residents, ward clerks, information technology personnel, privacy officers--to share the details of the implementation plan and record feedback. If any of these staff will be recorded during any of the consultations, then the RA will ask that they also sign an informed consent form. After the interviews have been completed, the local site coordinators, with support from the PI, research team, and RAs, will address the issues of evidence, context, and facilitation generated through these interviews. Only after the implementation considerations have been addressed will phase 2 begin. To capitalise on the implementation knowledge gained at each location, the phase 1 PI visit and oncologist interviews will begin at the second location only after phase 2 has been completed at the first location.

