#### Phase 3: postimplementation

At approximately two months following the participation of the final patient at each location, the PI will travel to the location to attend the weekly disease group (breast, prostate/genitourinary) meeting or a similar meeting at which the staff categories (oncologists, nurses, clerks) involved in the implementation are likely to be represented. The purpose of this meeting will be to solicit feedback regarding the successes and challenges realised during the implementation phase. This meeting will also be recorded, transcribed, and analysed for identification of salient points. The patient focus group described above and the oncology staff meeting will be held on consecutive days. The patient focus group will be held on the first day so that the salient points from the focus group can be shared with staff at the disease type meeting the next day.

At one month following the last of the postimplementation review meetings with oncology staff, a meeting of the research team will be held to review the findings of the postimplementation staff meetings, patient focus groups, and data from the DRUSSI and to complete a conceptual framework that describes the interrelationship of evidentiary, contextual, and facilitative factors that are fundamental to the successful transfer and uptake of the consultation-recording intervention. The development of the conceptual framework will be guided by the PARIHS KT framework, diffusion of innovation theory, and social network theory and will be the most important task of this meeting.

This team meeting will also serve to review, revise, and delineate the execution of the strategy for the dissemination of the study findings. At present, the team has developed a seven-point dissemination strategy:

1. Grand rounds: Present the results of the study (DRUSSI findings, findings from the patient focus groups and oncology staff review meetings) at grand rounds or a similar forum at each implementation site.

2. Café Scientifique: Most universities have information events that bring academics, clinicians, patients, and the public together. We will present our findings at these events at the Universities of Calgary, British Columbia, and Manitoba.

3. Peer-reviewed journal publication: Submit manuscripts of our research findings to peer-reviewed journals.

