The sources of data for analysis will include oncology staff personal interviews and focus group interviews (preimplementation, implementation, and postimplementation), semistructured patient interviews (DRUSSI), and the patient benefit letters to the oncologists/nurses. All of the transcribed focus group interviews (patient and staff) and the individual staff interviews will be analysed according to the following qualitative analytic procedures: The study PI, local PI, and the local RA at each location will perform a latent content analysis of the transcripts for that location, coding the transcripts for common themes. Having three coders will help to minimize coding bias. A conference call involving the three coders will take place at approximately one-third of the way through the implementation phase at each site at each location for the purpose of achieving coding consistency of the data gathered to that point, discussing emerging themes, and deciding whether method changes are warranted, including possible modification of the DRUSSI (the telephone administration of the DRUSSI will preclude recording, but the RA will be instructed to take detailed notes that will be analysed and summarised into salient points). A second conference call will occur two-thirds into the implementation phase for the same purpose. A final conference call will take place after the last interview has been coded. The basic unit of coding will be a 'meaning unit', which may be a few words to a few sentences in length. Using open coding [38], the goal will be to arrive at 'distinct meaning units' by applying a constant comparative analysis [39,40] to new open codes that are applied, so that categories of similar codes are eventually generated. The next level of coding will be 'theoretical coding', whereby meaningful connections between categories are formed. Recordings will be transcribed as soon as possible, followed by the analysis of the transcripts within the following one to three weeks to enable timely modifications to method.

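### A patient advocate is invited to promote the intervention in the same recorded focus group that collects patients' feedback on it

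*Protocol article*

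**What the plan says.** Phase 2 plans a focus group of participating patients at each location, after the last patient interview there. Its purpose is stated as follows: "The goal of the focus group is to provide feedback and learn more about the patients' consultation-recording experiences". The next sentence says that a local patient advocate for the disease "will be invited to attend the focus group in an effort to promote the intervention". On conduct, the article says: "The RA and the PI will lead the focus groups; each focus group will be recorded and transcribed". Under Data management and analysis, all patient and staff focus group transcripts go to latent content analysis by three coders.

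Phase 3 adds a staff meeting the day after the patient session. Its aim is again evaluative: "The purpose of this meeting will be to solicit feedback regarding the successes and challenges realised during the implementation phase". It is a data source too: "This meeting will also be recorded, transcribed, and analysed for identification of salient points". The patient session is placed first "so that the salient points from the focus group can be shared with staff at the disease type meeting the next day".

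**The concern.** A session that collects evaluation data should not also contain an activity meant to move opinion in one direction. Here the two purposes stand in consecutive sentences and nothing separates them. Patients with a poor or indifferent experience may hold back when someone is present to support the intervention.

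Three objectives are exposed. Objective 1 needs the factors that impede uptake as well as those that help it. Objective 2 asks whether patients can articulate benefits, so an answer given in a promotional setting is weaker evidence. Objective 3 builds the conceptual framework from the coded patient and staff transcripts. The staff meeting raises a related, smaller question of order, because staff may hear the patients' points before giving their own views.

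**Working it through.** No arithmetic applies. The article gives no sample size, rate or error level on this point, so the check sets its statements side by side.

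1. **Purpose against attendance (Phase 2).** The goal is patient feedback, and the patient advocate's stated reason for attending is promotion. Both belong to one session. The article does not say that the patient advocate arrives later, leaves early or stays silent, nor how the patient advocate's words are treated in the transcript.

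2. **Is the session data?** Yes. It is recorded and transcribed (Phase 2), coded (Data management and analysis), and in hand when the framework is drafted.

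3. **Is there another patient source?** Yes, in part. The Digital Recording Use Semi-Structured Interview (DRUSSI) is given by telephone at two and seven days after the consultation, before any focus group, so the patient advocate cannot influence it. However, Data management and analysis says that telephone administration rules out recording, so this source consists of the research associate's notes. The focus groups are therefore the only patient interviews with a verbatim record.

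4. **Does a stated safeguard cover this?** The named control is the use of three coders. That addresses how words are coded, not what participants choose to say. Two of the three coder roles, the study PI and the local research associate, also lead the focus groups.

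5. **How many sessions?** The oncologist sample section counts four locations, so one focus group at each gives four. Attendance is by invitation, so four is the most that could be affected, not the number that will be.

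6. **Staff meeting.** Staff feedback is sought in a session designed to receive the patients' points from the day before, and no order within the meeting is given. Transcription is to happen as soon as possible, "followed by the analysis of the transcripts within the following one to three weeks". Points shared one day after the focus group would, on that timetable, not yet be coded, although Phase 2 ties salient points to transcript review. They would most plausibly be the session leaders' impressions.

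**The case against.** **The patient advocate may only listen.** The sentence does not say that the patient advocate will speak. The background treats advocacy groups as allies in dissemination, so the patient advocate might attend to hear patients and promote recordings elsewhere afterwards. This reading is fair, and it rules out saying that patients will be told what to value. It does not remove the point, because patients would still speak in front of a person invited as a promoter.

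**Promotion is part of the strategy.** The article deliberately treats patients and their advocacy groups as agents of change. That stands, and nothing here asks for that component to be removed. The issue is only its position inside data collection.

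**Agenda order belongs in a moderator guide.** This is a condensed article, and it says that exact procedures follow from phase 1. Silence on order is therefore not an error in itself. But the promotional purpose of attendance is stated, not omitted.

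**The staff meeting is not clearly biased toward benefit.** Salient points may include problems. Staff will also already have received letters from willing patients during phase 2, so reversing the agenda would not make their feedback independent of patient reports. Both objections stand and leave only a modest case for asking staff first.

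**Two stronger readings are not supported.** A reader might infer that barriers will be under-reported in all the main sources. The DRUSSI interviews, the staff check-in after five patients and the coordinator's log book are not exposed to the patient advocate. A reader might also see the same fault in phase 1, where "the results of the prestudy contextual readiness assessment will be shared" before feedback is sought. That assessment included barriers and differing views on benefit, and the feedback sought is on the plan itself, which must be presented first.

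**Conclusion.** The point holds for the patient focus group: an activity with a stated promotional purpose is placed, without separation, in a session whose transcript is evaluation data. The likely direction is toward fewer negative accounts. That is an inference from the patient advocate's stated role, and it assumes that the patient advocate accepts the invitation and is present while patients give feedback. The size is unknown. The reach is at most four focus groups, with the DRUSSI record intact.

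For the staff meeting a secondary point remains. Staff views may be given after hearing patient points that are not yet coded, so the two sources are less separate than they could be. No direction can be assigned to that.

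**What to change.** **Main change, Phase 2.** State that the recorded feedback part of each focus group is completed and closed before the patient advocate joins. If recording continues, mark the point of entry in the transcript so that later material can be recognised in coding.

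**Secondary change, Phase 3.** At the staff meeting, ask for successes and challenges first and share the patients' points afterwards. Tag the change-over in the transcript and code both parts with that tag. Discarding the second part would work against the article's aim of identifying barriers and facilitators as exhaustively as possible. Describe the next-day patient points as preliminary and uncoded.

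**Cost.** A fixed agenda order in two kinds of meeting and a marker in each transcript. No added visits, staff or patients are needed, and the patient advocate's role and the feedback to staff are both kept. The patient advocate would no longer hear the patients' feedback live, but the session leaders could summarise it when the patient advocate joins.

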#### Phase 3: postimplementation

At approximately two months following the participation of the final patient at each location, the PI will travel to the location to attend the weekly disease group (breast, prostate/genitourinary) meeting or a similar meeting at which the staff categories (oncologists, nurses, clerks) involved in the implementation are likely to be represented. The purpose of this meeting will be to solicit feedback regarding the successes and challenges realised during the implementation phase. This meeting will also be recorded, transcribed, and analysed for identification of salient points. The patient focus group described above and the oncology staff meeting will be held on consecutive days. The patient focus group will be held on the first day so that the salient points from the focus group can be shared with staff at the disease type meeting the next day.

At one month following the last of the postimplementation review meetings with oncology staff, a meeting of the research team will be held to review the findings of the postimplementation staff meetings, patient focus groups, and data from the DRUSSI and to complete a conceptual framework that describes the interrelationship of evidentiary, contextual, and facilitative factors that are fundamental to the successful transfer and uptake of the consultation-recording intervention. The development of the conceptual framework will be guided by the PARIHS KT framework, diffusion of innovation theory, and social network theory and will be the most important task of this meeting.

This team meeting will also serve to review, revise, and delineate the execution of the strategy for the dissemination of the study findings. At present, the team has developed a seven-point dissemination strategy:

1. Grand rounds: Present the results of the study (DRUSSI findings, findings from the patient focus groups and oncology staff review meetings) at grand rounds or a similar forum at each implementation site.

2. Café Scientifique: Most universities have information events that bring academics, clinicians, patients, and the public together. We will present our findings at these events at the Universities of Calgary, British Columbia, and Manitoba.

3. Peer-reviewed journal publication: Submit manuscripts of our research findings to peer-reviewed journals.

4. Media: With the support of the Communications Officers at the British Columbia Cancer Agency, the Tom Baker Cancer Centre, and CancerCare Manitoba, local and national print, radio, and television news media will be contacted. The popular media (television and magazines) will also be contacted in the hope of reaching as many of the target audience of potential cancer patients as possible.

5. Book chapter: Drs. [name] and [name] recently published a book chapter titled "Audio-recording important consultations for patients and their families--putting evidence into practice" [37] to help establish consultation recordings as a valuable clinical practice. The value of consultation recordings and the use of theoretical frameworks to address implementation challenges are conveyed in this chapter.

6. Conference presentations: Present the research findings at local meetings and national and international conferences.

7. Symposium: Organise a one-day symposium, at which the findings will be discussed with a broad mix of purposefully selected stakeholders (academics, clinicians, patients, patient advocates) to establish a national direction for research in the area of consultation-recording use in oncology.

### Data management and analysis

A relational database will be created using SPSS for Windows (Version 15; SPSS Inc., Chicago, IL, USA) to store quantitative data. This database; copies of all consultation recordings; all patient sociodemographic, illness, and interview data; and oncologist/nurse interview data will be stored on a central server at the PI's institution, with access limited to specific users at the discretion of the PI; this server is backed up daily. All recordings will be sent to the PI via a key-protected internet website. Patient names will not be stored in data files (hard copy records linking patient names with computer identifiers will be stored in a separate location). Regular meetings of the PI, data manager, project staff, and biostatistical consultant, if necessary, will be held to review progress and discuss concerns.

The sources of data for analysis will include oncology staff personal interviews and focus group interviews (preimplementation, implementation, and postimplementation), semistructured patient interviews (DRUSSI), and the patient benefit letters to the oncologists/nurses. All of the transcribed focus group interviews (patient and staff) and the individual staff interviews will be analysed according to the following qualitative analytic procedures: The study PI, local PI, and the local RA at each location will perform a latent content analysis of the transcripts for that location, coding the transcripts for common themes. Having three coders will help to minimize coding bias. A conference call involving the three coders will take place at approximately one-third of the way through the implementation phase at each site at each location for the purpose of achieving coding consistency of the data gathered to that point, discussing emerging themes, and deciding whether method changes are warranted, including possible modification of the DRUSSI (the telephone administration of the DRUSSI will preclude recording, but the RA will be instructed to take detailed notes that will be analysed and summarised into salient points). A second conference call will occur two-thirds into the implementation phase for the same purpose. A final conference call will take place after the last interview has been coded. The basic unit of coding will be a 'meaning unit', which may be a few words to a few sentences in length. Using open coding [38], the goal will be to arrive at 'distinct meaning units' by applying a constant comparative analysis [39,40] to new open codes that are applied, so that categories of similar codes are eventually generated. The next level of coding will be 'theoretical coding', whereby meaningful connections between categories are formed. Recordings will be transcribed as soon as possible, followed by the analysis of the transcripts within the following one to three weeks to enable timely modifications to method.

The development of the conceptual framework of consultation-recording implementation will occur during the postimplementation phase according to established criteria: Prior to the postimplementation team meeting, the PI and each local PI and RA (seven individuals in total) will work separately to generate the framework. With the analysis of the transcripts of the patient and staff qualitative data in hand, each individual will first use the PARIHS framework as a starting template to which the themes and text exemplars will be fitted. Where an obvious fit of the data to the framework does not exist, the framework will be modified or expanded. Second, each individual will fit the qualitative findings of the oncology staff data to the diffusion of innovation theory and produce a summary of how this theory can be used to explain the implementation of consultation-recording practice. Third, each individual will attempt to build a comprehensive explanation of consultation-recording use that incorporates the PARIHS framework, diffusion of innovation theory, and social network theory. At the team meeting, the draft frameworks generated by these seven individuals will be reviewed by the entire research team. The final product will be a comprehensive conceptual framework of consultation-recording transfer and uptake that has a solid theoretical and empirical foundation.

